**Inclusion criteria:**

- 1) Voluntarily participate and sign the informed consent form;
- 2) Age between 18 and 75 years, any gender;
- 3) Histologically or cytologically confirmed pancreatic cancer or biliary tract tumor (TNM stage: stage IIIb/IV); failure of  $\geq 1$  line of treatment or intolerance to systemic therapy toxicity; presence of at least one measurable lesion based on Response Evaluation Criteria in Solid Tumors (RECIST) version 1.1;
- 4) Expected survival period of  $\geq 3$  months;
- 5) Eastern Cooperative Oncology Group (ECOG) performance status of 0-1;
- 6) Sufficient organ and bone marrow function, defined as follows:
  - a) Absolute neutrophil count (ANC)  $\geq 1,500/\text{mm}^3$  ( $1.5 \times 10^9/\text{L}$ );
  - b) Platelet count (PLT)  $\geq 100,000/\text{mm}^3$  ( $100 \times 10^9/\text{L}$ );
  - c) Hemoglobin (Hb)  $\geq 9$  g/dL (90 g/L);
  - d) Serum albumin  $\geq 2.8$  g/dL;
  - e) Serum creatinine  $\leq 1.5$  times the upper limit of normal (ULN) or creatinine clearance  $\geq 50$  ml/min;
  - f) Total bilirubin (TB)  $\leq 1.5 \times \text{ULN}$ , or TB  $> 1.5 \times \text{ULN}$  with direct bilirubin (DBil)  $\leq 1 \times \text{ULN}$  for liver metastasis patients or liver cancer patients, which should be  $\leq 2 \times \text{ULN}$ ;

- g) Aspartate aminotransferase (AST/SGOT) or alanine aminotransferase (ALT/SGPT) levels  $\leq 2.5 \times \text{ULN}$ , or  $\leq 5 \times \text{ULN}$  for liver metastasis patients or liver cancer patients;
  - h) Left ventricular ejection fraction (LVEF)  $\geq 50\%$ ; QTc  $< 450$  ms for males,  $< 470$  ms for females;
- 7) Patients not receiving anticoagulant therapy should have international normalized ratio (INR)  $\leq 1.5$  and activated partial thromboplastin time (APTT)  $\leq 1.5$  times the upper limit of normal. Patients receiving full-dose or extra-gastrointestinal anticoagulant therapy can enter the clinical trial if the anticoagulant dose has been stable for at least 2 weeks before entering the study and the coagulation test results are within the range allowed by local treatment restrictions;
  - 8) Women of childbearing potential must undergo a pregnancy test within 2 weeks before starting study medication, and the result must be negative. They must also agree to use a medically accepted highly effective contraceptive method during the study period and for 3 months after the last administration of the study drug. For male participants with female partners of childbearing potential, surgical sterilization is required, or they must agree to use an effective contraceptive method during the study period and for 3 months after the last study drug administration;
  - 9) Expected good compliance and willingness to cooperate with the study requirements.

**Exclusion criteria:**

- 1) Previous treatment with immune therapy targeting PD-1, PD-L1, CTLA4, or other immune therapies;
- 2) Previous treatment with TGF- $\beta$  inhibitors;
- 3) Known allergy to the study drug or any of its excipients, or a history of severe allergic reactions to other monoclonal antibodies;
- 4) Treatment received prior to the first study treatment, including:
  - a) Major surgery within 28 days prior to the first study drug treatment (except for diagnostic biopsies);
  - b) Use of immunosuppressive drugs within 7 days prior to the first study drug treatment, excluding nasal and inhaled corticosteroids or physiologic doses of systemic corticosteroid hormones (i.e., not exceeding 10 mg/day prednisone or its equivalent);

- c) Use of immunomodulatory drugs within 3 weeks prior to the first study drug treatment (e.g., thymosin, interferon, interleukins);
  - d) Receipt of attenuated live vaccines within 28 days prior to the first study drug treatment or planned vaccination with attenuated live vaccines during the study and within 60 days after the end of study drug treatment;
  - e) Receipt of antitumor treatment within 28 days prior to the first study drug treatment, except for cases where the interval between the last chemotherapy is at least 2 weeks or five half-lives (whichever is shorter), or the interval between the last targeted therapy is at least five half-lives;
- 5) Known uncontrolled or symptomatic central nervous system (CNS) metastases;
  - 6) Symptomatic, disseminated, and short-term life-threatening complications risk in advanced patients (including those with uncontrollable large effusions [pleural, pericardial, or abdominal]);
  - 7) Within the past 2 years, a history of other active malignancies, except for the following conditions that have been locally treated and cured: basal cell carcinoma or squamous cell carcinoma of the skin, superficial bladder carcinoma, cervical carcinoma in situ, intraductal breast carcinoma, and papillary thyroid carcinoma;
  - 8) Presence of any active autoimmune disease or a history of autoimmune disease with an anticipated relapse;
  - 9) Known history of allogeneic organ transplantation or allogeneic hematopoietic stem cell transplantation;
  - 10) Human immunodeficiency virus (HIV) infection or known acquired immunodeficiency syndrome (AIDS), untreated active hepatitis (hepatitis B, defined as positive hepatitis B surface antigen [HBsAg] and abnormal liver function with HBV-DNA  $\geq 500$  IU/ml; hepatitis C, defined as positive hepatitis C antibody [HCV-Ab] and detectable HCV-RNA above the limit of detection with abnormal liver function) or concurrent co-infection with hepatitis B and hepatitis C;
  - 11) Occurrence within the past 6 months before entering the study of: myocardial infarction, severe/unstable angina, New York Heart Association (NYHA) class II or higher heart failure, and clinically significant supraventricular or ventricular arrhythmias requiring clinical intervention; poorly controlled hypertension (systolic blood pressure persistently  $\geq 150$  mmHg or diastolic blood pressure  $\geq 100$  mmHg);

- 12) Use of systemic antibiotics for  $\geq 7$  days within 4 weeks before the first study drug administration or presence of unexplained fever  $>38.5^{\circ}\text{C}$  during the screening period or before the first study drug administration (fever due to tumor causes can be included according to the investigator's judgment);
- 13) History of gastrointestinal bleeding within the past 6 months or a tendency toward gastrointestinal bleeding, such as esophageal varices, active ulcer lesion, or fecal occult blood  $\geq(++)$  (patients with fecal occult blood (+) need to undergo gastroscopy);
- 14) Urine protein  $\geq(++)$  or 24-hour urinary protein  $> 1.0$  g;
- 15) Inability to swallow the study drug or the presence of factors affecting drug administration and absorption, such as chronic diarrhea (including, but not limited to, irritable bowel syndrome, Crohn's disease, and ulcerative colitis) and intestinal obstruction;
- 16) Pregnant or lactating women, or female participants of childbearing potential unwilling to use effective contraceptive measures;
- 17) Known history of neurological or psychiatric disorders, including epilepsy and dementia; known history of substance abuse or drug addiction;
- 18) Participation in any other drug clinical trial within 4 weeks before the first study drug administration or within 5 half-lives since the last study drug administration;
- 19) Presence of other severe physical or laboratory abnormalities that may increase the risk of participation in the study or interfere with study results, as determined by the investigator.

**Treatment termination  
criteria**

If any of the following events occur, the patient must terminate the study treatment:

- 1) The subject requests to discontinue the study drug treatment;
- 2) Poor compliance of the subject, not adhering to the study drug administration as per the protocol;
- 3) Occurrence of pregnancy in the subject during the course of the study;
- 4) Disease progression confirmed by the investigator based on the assessment of efficacy;
- 5) Even with dose adjustments, the subject remains unable to tolerate toxicity or experiences adverse events, laboratory abnormalities, or

concurrent diseases that, according to the investigator's judgment, make continued participation in the study not in the best interest of the subject;

- 6) Comprehensive deterioration of the subject's health, rendering them unable to continue participating in the trial;
- 7) Significant protocol deviations discovered after enrollment and confirmed by the investigator;
- 8) Other reasons as determined by the investigator that make it impossible to continue the study treatment.

**Study withdrawal**

Reasons for the subject's withdrawal from the study may include:

**criteria**

- 1) Subject's voluntary withdrawal of informed consent and refusal for further follow-up;
- 2) Other circumstances deemed necessary by the investigator for the subject to withdraw from the study;
- 3) Significant protocol design errors discovered during the conduct of the study;
- 4) Lost to follow-up;
- 5) Subject's death;
- 6) Premature termination of the clinical trial by the sponsor or ethics committee;

**Safety evaluation**

Adverse events severity will be assessed according to the CTCAE v5.0 standard. During the trial, an adverse event record form should be accurately filled out, including the time of occurrence, severity, duration, measures taken, and outcome of the adverse events.

**criteria**

**Efficacy assessment**

Subjects will undergo imaging evaluation every 2 cycles (6 weeks) after enrollment. Tumor response assessment will be performed based on RECIST 1.1 criteria. Subjects with a partial response (PR) or complete response (CR) need to undergo efficacy confirmation 4 weeks later.

**Statistical methods**

The main results of this trial will primarily use descriptive statistical methods. For continuous data, mean, standard deviation, median, maximum, minimum values will be presented, while for categorical data, frequency (proportion), rate, and confidence intervals will be provided.

#### Safety analysis:

Safety analysis will focus on descriptive statistics, analyzing adverse events, serious adverse events, and adverse reactions (where adverse reactions are defined as “definitely related/probably related/indeterminate related to the study drug”) occurring in each dose group. Laboratory test results will be described for cases where abnormalities are observed after treatment, which were normal before the study.

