| Objective          | Evaluation of the efficacy and safety of SHR-1701 in combination with famitinib for the treatment of advanced pancreatic cancer and biliary tract tumors                                                                                                                                                                                                                                                                                                                                                                                                                                                                                                                   |
| Endpoint           | 
Primary Endpoint:
 
Objective Response Rate (ORR) based on RECIST 1.1 criteria.
 
Secondary Endpoints:
 
(1) Efficacy Measures:
 

1. Disease Control Rate (DCR) based on RECIST 1.1 criteria.

2. Progression-Free Survival (PFS) based on RECIST 1.1 criteria.

3. Overall Survival (OS).

4. Quality of Life (QoL) assessed using the EORTC QLQ-C30 questionnaire.

 
(2) Safety Measures:
 
Including vital signs, laboratory parameters, Adverse Events (AE), Serious Adverse Events (SAE), drug-related AE and SAE.
 
(3) Biomarker Exploration.
 |
| Procedures         | This study adopts a Simon's two-stage design. Subjects are administered SHR-1701 (30mg/kg, intravenous, once every 3 weeks) in combination with famitinib (20mg, orally, once daily). The initial famitinib dose may be adjusted to 15mg based on the subject's previous treatment tolerance and                                                                                                                                                                                                                                                                                                                                                                           |

current condition. Treatment is administered in cycles of three weeks each, continuously until a treatment termination criterion is met or the subject withdraws from the study. If disease progression per RECIST 1.1 occurs, subjects may continue study treatment at the investigator's discretion if there is potential clinical benefit, acceptable safety, and patient consent.

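### The only laboratory-specific analysis rule covers normal-to-abnormal changes, although eligibility admits patients whose liver and renal values are already above normal

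*Protocol*

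**What the plan says.** The Safety analysis paragraph of the Protocol Abstract has one sentence on laboratory data: "Laboratory test results will be described for cases where abnormalities are observed after treatment, which were normal before the study". It sets two conditions, a normal value before the study and an abnormal one after treatment.

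The Endpoint row lists the safety measures without any baseline condition: "Including vital signs, laboratory parameters, Adverse Events (AE), Serious Adverse Events (SAE), drug-related AE and SAE". Efficacy and safety together form the stated objective.

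Inclusion criterion 6 is introduced by "Sufficient organ and bone marrow function, defined as follows". Several of its limits lie above the upper limit of normal. For the transaminases it reads "Aspartate aminotransferase (AST/SGOT) or alanine aminotransferase (ALT/SGPT) levels $\leq 2.5 \times \text{ULN}$ , or $\leq 5 \times \text{ULN}$ for liver metastasis patients", and the higher limit also applies to liver cancer patients. Bilirubin and creatinine limits are likewise set as multiples of ULN greater than 1.

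Three other statements bear on the point. Safety evaluation criteria has adverse events graded by CTCAE v5.0. Safety analysis describes adverse events, serious adverse events and adverse reactions with no condition on baseline. Statistical methods gives general summaries for continuous data (mean, standard deviation, median, maximum, minimum).

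**The concern.** A rule limited to patients who start normal suits a population with normal entry values. This trial's own entry limits let patients in with abnormal ones. For them the rule has no category: however far the value worsens, the first condition fails.

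Laboratory parameters are listed as a safety measure alongside adverse events, so a reader would expect the laboratory analysis to cover all treated patients. If an SAP follows the sentence as written, it inherits the gap. At stake is the completeness of the laboratory safety description, mainly for liver and renal function. The primary endpoint, ORR, is not affected.

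**Working it through.** There is no figure in the plan to reproduce. The check sets the rule beside the entry limits and then asks what other part of the plan would pick up the worsening.

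**Step 1. Which entry values fail the rule's first condition?** (Inclusion criterion 6)

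| Parameter | Entry limit | Can a patient enter abnormal? |
|---|---|---|
| AST/ALT | ≤ 2.5 × ULN; ≤ 5 × ULN with liver metastasis or liver cancer | Yes, by definition |
| Total bilirubin | ≤ 1.5 × ULN; up to 2 × ULN in the liver groups | Yes, by definition |
| Creatinine | ≤ 1.5 × ULN, or creatinine clearance ≥ 50 ml/min | Yes, by definition |
| Hemoglobin | ≥ 9 g/dL | Yes, if usual reference ranges apply (assumption) |
| Albumin | ≥ 2.8 g/dL | Yes, if usual reference ranges apply (assumption) |

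The first three rows need no outside source: a value above ULN is not normal. The last two need a reference range that the document does not print.

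**Step 2. Apply the rule to two patients.**

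- Patient A has liver metastasis, enters with ALT 3 × ULN (allowed, since 3 ≤ 5) and rises to 10 × ULN. Normal before: no. Not described.
- Patient B enters with normal ALT and rises to just above ULN. Normal before: yes; abnormal after: yes. Described.

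The larger change is left out and the smaller one is kept.

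**Step 3. What else would show Patient A?**

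- Adverse event tables, if the investigator records the rise as an event. No part of the document says when a laboratory change must be recorded as one.
- The general summaries for continuous data, if applied to laboratory values. A mean or median does not identify who worsened. A maximum shows one extreme value without its baseline.
- A shift from baseline grade, or a worst on-treatment grade for all patients: not stated anywhere.

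**Step 4. Illustrative size.** The document gives no baseline distribution. Let *N* be the number treated and *p* the assumed share abnormal at baseline on one parameter. The number who cannot appear in that parameter's description is *N* × *p*.

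| Assumed *p* | *N* = 60 (planned total) | *N* = 30 (Stage I, 15 + 15) |
|---|---|---|
| 20% | 60 × 0.20 = 12 | 30 × 0.20 = 6 |
| 40% | 60 × 0.40 = 24 | 30 × 0.40 = 12 |
| 60% | 60 × 0.60 = 36 | 30 × 0.60 = 18 |

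**Step 5. Does this bias a reported rate?** Suppose the true worsening rate *w* is the same whatever the baseline. The rule then captures *N*(1 − *p*)*w* cases.

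- Divided by all treated: *N*(1 − *p*)*w* / *N* = (1 − *p*)*w*, too low by the fraction *p*.
- Divided by those normal at baseline: *N*(1 − *p*)*w* / [*N*(1 − *p*)] = *w*, with no understatement.

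The protocol fixes no denominator, so no percentage understatement can be attached to the rule.

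**The case against.** The strongest reply has four parts.

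- **The sentence is not exclusive.** It does not say that other laboratory results will go undescribed. Read with the unrestricted listing under Endpoint and the general rule for continuous data, it could be an extra description on top of ordinary summaries. This stands as far as it goes, and it rules out claiming that patients with abnormal baselines vanish from every summary. But the only rule written for laboratory data still omits them, and general means and maxima do not show worsening patient by patient.
- **Adverse event reporting catches what matters.** Marked changes, such as hemoglobin falling from 9.5 to 6 g/dL, could be expected to be recorded and graded, and those tables carry no baseline condition. A reader might infer that the rule hides laboratory toxicity; the document does not support that, because this route stays open. It does depend on the change being recorded as an event, and the protocol lists laboratory parameters as a measure in their own right.
- **The size is unknown.** A reader might infer that many patients are affected, or that toxicity is understated by a definite percentage. Neither is supported: entry limits show who may enter, not how many do, and any understatement of a rate depends on the denominator. This stands in full.
- **Shift tables belong in an SAP.** Their layout does. However, the protocol has not left the matter open; it states a rule, and the rule does not fit the population it admits.

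**Conclusion.** The point holds as a badly fixed rule. The sole laboratory-specific analysis sentence covers patients who go from normal to abnormal, while the inclusion criteria admit AST/ALT, bilirubin and creatinine above ULN. Worsening from such a baseline is outside the laboratory description and is visible only through adverse event reporting or general descriptive statistics.

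For liver and renal tests this follows from the document alone. Extending it to hemoglobin and albumin assumes usual reference ranges. The number of patients is not known; 12 to 36 of 60 per parameter corresponds to an assumed 20% to 60% and is not an estimate. The document does not support a statement that laboratory toxicity is concealed, or that it is understated by a particular fraction.

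The sponsor should correct this, but it is a safety-reporting matter: no decision rule, sample size or error rate depends on it.

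**What to change.** Replace the laboratory sentence in Safety analysis with a rule along these lines: for every treated patient and each graded laboratory parameter, tabulate the baseline CTCAE v5.0 grade against the worst post-baseline grade. Count any increase of at least 1 grade and every new grade ≥3 value, whatever the baseline. Keep the normal-to-abnormal count as one row of that table, and state the denominator for each row.

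The grading scale is the one the protocol already uses for adverse events, and laboratory parameters are already a listed safety measure. The cost is one amended sentence and a few extra tables.

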#### Efficacy analysis:

Efficacy analysis will estimate the objective response rate (ORR), disease control rate (DCR), and other efficacy endpoints with point estimates and provide 95% confidence intervals representing the overall population using the Kaplan-Meier method. Survival curves will be plotted for median progression-free survival (PFS) and median overall survival (OS). Other secondary efficacy measures such as quality of life will be analyzed descriptively.

Expected first subject enrollment date: August 2020

Expected last subject enrollment date: February 2022

Expected study completion date: February 2023

#### **Study duration**
